### Interventions

We have established several field sites in an urban slum (Mirpur district of Dhaka). The Kurigram field site has been established in collaboration with the Terre des Hommes NGO. The post-SAM MAM study will enroll participants living in both Mirpur and Kurigram while the MAM study will be conducted in Mirpur. We have established a Food Processing Laboratory at the Mirpur and Kurigram field sites in order to freshly prepare the MDCF-2 and RUSF formulations each day prior to their distribution on that day to study participants.

Every child will be offered 25 g of the diet twice daily at the feeding center for the first 4 weeks. In the following month, the child will be offered 25 g of the diet at the feeding center and additional 25 g will be provided in a clean container to feed at home. In the third month, two separate containers containing 25 g diet will be provided every day to each enrolled child at participant’s home. Feeding information will be collected from mothers and amount consumed is determined from the weight of supplement remaining at the end of each feeding session.

In the stabilization phase of the post-SAM MAM trial, each child will be managed according to WHO/icddr,b guidelines [7]. This protocol includes programmed feeding, micronutrient supplementation, judicious rehydration, broad spectrum antibiotic treatment and prompt recognition and management of complications. Upon recovery from the stabilization phase, the child will receive a standard of care dietary protocol based upon the local diets Halwa and Khichuri. Upon graduation from SAM to MAM (edema-free WLZ < -2), children will be randomly assigned to one of the two arms.

The schedule for collection of anthropometric data and biological samples are noted in Fig. 1a, b. Children will be seen 1 month after cessation of treat for anthropometry and collection of fecal, blood and urine specimens and subsequently every 6 months for up to 4 years.

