**Methods:**

Two separate cohorts of 12–18-month-old children will be enrolled: 124 with primary MAM, and 124 with MAM after having been treated for severe acute malnutrition (post-SAM MAM). We have established several field sites in an urban slum located in the Mirpur district of Dhaka, Bangladesh and at a rural site, Kurigram in the north of Bangladesh. The two groups of children receiving MDCF-2 and RUSF will be compared at baseline (pre-intervention), after 1 month, at the end of intervention (3 months), 1 month after cessation of intervention, and every 6 months thereafter for 4 years.

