Failure to obtain informed written consent from parents/guardians	

Participants’ guardian/ caregiver who will provide written informed consent and participants who satisfy the inclusion/exclusion criteria will be randomized to one of the two treatment arms (MDCF-2, RUSF) using the permuted block randomization method with concealment to ensure that the allocation is not made before obtaining consent from parents/caregivers to participate in the study. A random allocation sequence will be generated using a computerized random allocation system for permuted block randomization to ensure comparable allocation number at a certain equally spaced points in the sequence of participant assignment. Parallel type of randomization will be used. Blocks of 2 and 4 will be constructed to reduce the predictability. Random assignment will be prepared in advance by an independent researcher from icddr b who has no involvement in the trial. Study staffs are blinded to random assignments.

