### Sample size calculation

Primary outcome measures will include rate of weight gain, change in weight and length; change in WLZ, change in MUAC, change in LAZ, morbidity, extent of repair of gut microbial community immaturity, and changes in the levels of key plasma biomarkers of host physiological state. We plan to include 124 participants (*n* = 62/treatment arm) for the primary MAM trial and for the post-SAM MAM trial. Recruitment of 124 participants will give 80% power at 5% significance level based on the change in WLZ scores of children from the recently completed pre-POC trial of different MDCFs. In the pre-POC trial of different MDCFs, the baseline WLZ score of children who received MDCF 2 was − 2.2 and after 1 month of supplementation was − 1.7. If we consider the WLZ − 2 at baseline and − 1.7 at end line, pooled standard deviation as 0.53, then the sample size would be 49 in each arm at 80% power and 5% level of significance. With 20% attrition, 62 enrolled children will be needed for each arm in each of the two trials.

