### Data analysis plan

The two groups of children receiving MDCF-2 and RUSF in each trial will be compared at baseline and at different time points as shown Fig. 1a, b. The clinical outcome variables will include rate of weight gain, anthropometric indices, and morbidity. We will perform t-test, Mann-Whitney test, Chi-Square test and Fisher’s exact test to compare the primary clinical outcome variables between the intervention arms. Multivariable linear regression will be employed to assess the role of the nutritional interventions to the anthropometric outcome. The data analyst will be blinded to the intervention arms.

Serially collected biospecimens will be analysed for (ii) changes in the plasma proteome (characterized by quantitative aptamer-based measurements of 5000 different proteins including those that are biomarkers and mediators of bone growth, metabolism, immune function, neurodevelopment and other aspects of physiologic status), fecal, plasma and urinary metabolomes (utilizing targeted and non-targeted mass spectrometry, including the products of metabolism carbohydrate components of the diet and of host metabolic health), (iii) repair of the gut microbiota (V4-16S rDNA amplicon sequencing to identify the abundances of ecogroup bacterial taxa and qPCR assays of the levels/diversity of common enteropathogens in fecal samples) and microbiome (shotgun sequencing of fecal DNA samples to characterize changes in the representation of microbial genes including those involved in the metabolism of various nutrients). A variety of computational tools, including those that allow for feature reduction [6, 10], will be applied to these multi-omic datasets to identify significant correlations between components of the microbiota/microbiome, proteome, metabolome and clinical parameters.

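### Post-SAM MAM trial: two contrasting sites, but no site stratum is named in the randomisation and the named primary tests take no account of site

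*Protocol article*

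**What the plan says.** All references are to the protocol article.

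- **Sites.** Under Interventions: "The post-SAM MAM study will enroll participants living in both Mirpur and Kurigram while the MAM study will be conducted in Mirpur". The abstract's Methods paragraph describes the settings as "an urban slum located in the Mirpur district of Dhaka, Bangladesh and at a rural site, Kurigram in the north of Bangladesh". So the Mirpur/Kurigram contrast arises only in the post-SAM MAM trial.
- **Randomisation** (Study design, paragraph after Table 1). Children are allocated "using the permuted block randomization method with concealment". The text continues: "A random allocation sequence will be generated using a computerized random allocation system for permuted block randomization". Block sizes are given: "Blocks of 2 and 4 will be constructed to reduce the predictability". An independent researcher prepares the assignments. No stratification factor is named, and separate lists by site are neither stated nor ruled out.
- **Analysis** (Data analysis plan). For the primary clinical outcomes: "We will perform t-test, Mann-Whitney test, Chi-Square test", together with Fisher's exact test. A multivariable linear regression follows for the anthropometric outcome, with no covariates listed. The multi-omic data are to be searched for correlations with clinical parameters.
- **Size** (Sample size calculation). Each trial is to enrol 62 children per arm, and the stated basis is: "Recruitment of 124 participants will give 80% power at 5% significance level based on the change in WLZ scores".

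**The concern.** Growth, morbidity and above all gut microbiota may differ between an urban slum and a rural district. The article gives no figures on this. If they do differ, site is a known source of variation that the named comparisons leave in the error term. Blocks running across both sites balance the arms overall but not within each site. A chance excess of one site in one arm then moves the observed arm difference.

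Stratification is part of the design and would normally be described beside block size, generation and concealment, all of which this paragraph covers.

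The regression does not close the gap. The Sample size calculation section also lists morbidity, microbiota repair and plasma biomarkers as primary outcomes, and no site-adjusted analysis is named for them. The correlation analyses are the most exposed, because randomisation does not protect them. If taxa, proteins and growth all differ by site, pooling the two sites can produce associations that merely reflect where the child lives.

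**Working it through.** **Inputs from the article:** planned difference 0.3 WLZ (−2 versus −1.7), SD 0.53, 5% significance, 80% power, 49 evaluable per arm, 20% attrition, 62 enrolled per arm, blocks of 2 and 4.

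**Assumptions, since the article gives neither figure:** share f of children from one site, 50% to 80%; difference D between sites in mean WLZ change, 0.1 to 0.3.

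**1. The plan's own figure.** n = 2 × [0.53 × (1.960 + 0.842) / 0.3]² = 48.99, so 49 per arm. 49 / 0.8 = 61.25, so 62. Both stated figures reproduce with a two-sided test.

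**2. Site imbalance under one unstratified sequence.** With randomly mixed arrivals, the SD of the between-arm difference in site share is about √[2f(1−f)/62], and 1.96 SD is:

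- f = 0.5: 17.6 percentage points
- f = 0.7: 16.1 points
- f = 0.8: 14.1 points

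A simulation of mixed blocks of 2 and 4 over 124 children (20,000 runs) gives 95th percentiles of 17.7, 16.1 and 14.5 points. A difference of 10 points or more occurs in 25%, 21% and 15% of runs. Separate lists by site bring the 95th percentile down to about 2 points.

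These figures are the unfavourable case. Small blocks also protect within site when children arrive in runs from one place. With f = 0.5, the 95th percentile is about 13 points for runs averaging 4 children, 10 for runs of 8 and 6 for runs of 20.

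**3. Effect on the estimate.** Shift = imbalance × D. At the 95th percentile this runs from 0.145 × 0.1 ≈ 0.01 to 0.177 × 0.3 ≈ 0.05 WLZ. The planned effect is 0.3, and the standard error of the arm difference at 49 per arm is 0.53 × √(2/49) = 0.107.

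**4. Effect on power.** Between-site variance is f(1−f)D², and power = Φ(0.3 / [SD × √(2/49)] − 1.96).

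- *If 0.53 is a within-site SD.* This is plausible, because the pilot on which the calculation rests was run in Mirpur only. The unadjusted SD is √(0.53² + f(1−f)D²).
  - f = 0.5, D = 0.3: SD 0.551, power 76.9%, 53 per arm needed.
  - f = 0.8, D = 0.1: SD 0.532, power 79.8%, 50 per arm needed.
  - A model with site returns the SD to 0.53 and power to 80%.
- *If 0.53 already contains the site difference.* The unadjusted test keeps 80.0%. Adjusting for site raises power to between 80.2% and 83.2%, or needs 46 to 49 per arm.

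Steps 3 and 4 describe the same error in two ways and must not be added together.

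**5. If separate site lists are used but the test ignores them.** The unadjusted standard error is then too large by a factor √[1 + f(1−f)D²/0.53²]. At f = 0.5 and D = 0.3, the actual two-sided error rate is 2 × [1 − Φ(1.96 × √1.080)] ≈ 4.2%. With an extreme site effect of 0.8 SD it is 2 × [1 − Φ(1.96 × √1.16)] ≈ 3.5%. The test is conservative, at some cost in power.

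**The case against.** The strongest reply is that the article is silent and excludes nothing. The randomisation paragraph serves two trials in generic wording, so its singular reference to a sequence is weak evidence against site lists. The regression may include site, and covariate lists are commonly left to a full protocol or analysis plan that is not shown. This stands. A reader might infer that neither the randomisation nor the analysis uses site, but the text supports only that neither is stated to do so.

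A reader might also infer that site imbalance would bias the result. It would not: under valid randomisation the unadjusted comparison is unbiased in expectation, and chance imbalance is added variance. Nor do site lists combined with an unadjusted test create a false-positive risk (step 5).

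It is fair to add that diets are made at each site but from ingredients bought at a single Dhaka market, and that the article does not say separate teams deliver them. Finally, enrolment began in November 2018, so new lists can reach only children not yet randomised.

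What the reply does not remove: the tests named for the primary clinical outcomes cannot take account of site as named, and the regression is confined to the anthropometric outcome.

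**Conclusion.** The point holds, at modest size, for the post-SAM MAM trial only. The primary MAM trial is conducted in Mirpur and is not affected by this contrast.

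For WLZ the loss is about 0 to 3 points of power, on assumed site shares of 50% to 80% and site differences of 0.1 to 0.3 WLZ, with 0.53 taken as a within-site SD. A much larger loss needs an extreme assumption: a site effect of 0.8 SD (0.42 WLZ, more than the whole planned treatment effect) with equal sites would give an SD of 0.53 × √1.16 = 0.571 and power of about 74%. The direction is secure. The size cannot be fixed from the article, which gives no site split and no site effect.

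The 15 to 18 point imbalance applies only to one unstratified sequence with randomly mixed arrivals. For the microbiota and protein correlations the size cannot be estimated, but there the issue is confounding by site, not only precision.

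**What to change.** For the post-SAM MAM trial:

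1. State whether allocation is stratified by site. If it is not, use a separate permuted-block list for each of Mirpur and Kurigram for children still to be randomised.
2. Make the primary between-arm comparison a model with arm and site (Mirpur/Kurigram) as fixed effects, for all children and under either form of allocation. Use a corresponding site-adjusted method for categorical outcomes such as morbidity.
3. Add the site term to the microbiota and protein analyses and to the correlation analyses.
4. Record this before the blinded analyst begins the comparisons.

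The cost is one model term and, where needed, one more list from the independent researcher. The sample size stays at 62 per arm.

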### Production of MDCF-2 and RUSF, and quality control measures

RUSF is composed of rice, lentil, sugar, soybean oil, and skimmed milk powder mixed with vitamin mineral premix. MDCF-2 is composed of chickpea flour, peanut flour, soy flour, green banana, sugar, soybean oil and vitamin-mineral premix (Table 2). Both study diets will be prepared in the icddr,b Food Processing Laboratory or nutrition centre established at each site. MDCF-2 is similar in energy density and micronutrient content to ready-to-use supplementary foods used for treatment of MAM in Bangladesh and other countries; it meets all safety and other WHO requirements for a complementary/supplementary food for 12–18-month-old children with MAM. Organoleptic acceptability was confirmed previously in the pre-POC study. Table 2 provides details about the composition, nutritional content of MDCF-2 and RUSF.

**Table 2 Tab2:** Composition of the study interventions

	MDCF 2 (g/100 g)	RUSF (g/100 g)
Components	Chickpea flour (10)	Rice (18.9)
	Peanut flour (10)	Lentil (21.5)
	Soybean flour (8)	Skimmed milk powder (10.5)
	Green banana (19)	–
	Sugar (29.8)	Sugar (17)
	Soybean oil (20)	Soybean oil (29)
	Micronutrient mix (3.14)	Micronutrient mix (3.14)
Protein	11.6	10.2
Fat	20.8	29.5
Carbohydrate	46.2	48.8
Fiber	4.5	4.7
Protein-Energy ratio	11.4	8.2
Fat-Energy ratio	46.0	53.6
Total Calories (per 100 g)	406.8	494.6

We will purchase all raw ingredients for the diets from a single local market in Dhaka; these ingredients will be used to formulate the diets at both field sites. The icddr,b Food Safety Laboratory will routinely culture random samples of the prepared diets on (Luria-Bertani, Mannitol Egg Yolk Polymyxin, Tryptic Soy Broth Agar) media to quantify viable bacteria (including tests for *Escherichia coli, Bacillus cereus, Staphylococci*), yeast and other fungi. Nutritional composition will be confirmed at the Institute of Nutrition, Mahidol University, Thailand using standard procedures.

### Anthropometry, data collection tools and quality control measures

Body weight will be measured to the nearest 1 g using the Dual-Purpose Baby Scale (Seca, West Midlands, UK). Mid upper arm circumference (MUAC) will be quantified with a MUAC tape. Standing height will be determined to the nearest 0.1 cm using a Stadiometer, and supine length will be defined to the nearest 0.1 cm using an Infantometer (Seca). All scales will be calibrated daily. At each assessment, 3 consecutive measurements will be taken and the average value will be recorded. Interrater consistency (kappa) will be determined at regular intervals [8].

### Collection, preparation and archiving of biological samples

Biospecimens will be collected before, during and after the intervention at the time points indicated in Fig. 1a, b. Venous blood will be collected in EDTA containing tubes from children and their mothers (2 mL and 5 mL, respectively). Plasma will be recovered after centrifugation, aliquoted into cryovials and the vials will be stored at -80 °C. After cleaning the genital area with alcohol pads, 2 mL of urine will be collected into a collection bag from children and 5 mL from their mothers. Following centrifugation, aliquots will be maintained at -80 °C in cryovials. Fecal samples will be collected in a sterile container, transferred by the field worker within 20 min of defecation into sterile 2 mL cryovials and immediately placed in Taylor Wharton CX300 dry cryoshippers that are pre-charged with liquid N2. Upon return to the laboratory, these vials will be stored at -80^o^ C.

### Data management and storage

Procedures for data management at icddr,b have been previously described [9]. An Excel-based program will be used for scheduling data and sample collection from each participant. Feeding information, including the total amount of MDCF-2 and RUSF consumed at each treatment session, and responses to a food frequency questionnaire, will be collected by the field research supervisors. Barcoded labels are used for all laboratory specimens. Unique codes are provided for each of study sites. All reports, study data collection and administrative forms are coded to maintain study participant confidentiality and for future reference. All study-related documents are kept in locked cabinets in locked rooms with restricted access.

### Data analysis plan

The two groups of children receiving MDCF-2 and RUSF in each trial will be compared at baseline and at different time points as shown Fig. 1a, b. The clinical outcome variables will include rate of weight gain, anthropometric indices, and morbidity. We will perform t-test, Mann-Whitney test, Chi-Square test and Fisher’s exact test to compare the primary clinical outcome variables between the intervention arms. Multivariable linear regression will be employed to assess the role of the nutritional interventions to the anthropometric outcome. The data analyst will be blinded to the intervention arms.

Serially collected biospecimens will be analysed for (ii) changes in the plasma proteome (characterized by quantitative aptamer-based measurements of 5000 different proteins including those that are biomarkers and mediators of bone growth, metabolism, immune function, neurodevelopment and other aspects of physiologic status), fecal, plasma and urinary metabolomes (utilizing targeted and non-targeted mass spectrometry, including the products of metabolism carbohydrate components of the diet and of host metabolic health), (iii) repair of the gut microbiota (V4-16S rDNA amplicon sequencing to identify the abundances of ecogroup bacterial taxa and qPCR assays of the levels/diversity of common enteropathogens in fecal samples) and microbiome (shotgun sequencing of fecal DNA samples to characterize changes in the representation of microbial genes including those involved in the metabolism of various nutrients). A variety of computational tools, including those that allow for feature reduction [6, 10], will be applied to these multi-omic datasets to identify significant correlations between components of the microbiota/microbiome, proteome, metabolome and clinical parameters.

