The pre-POC study involved small numbers of children (15–17/arm) and the 1-month long intervention was too brief to determine whether a substantial and durable repair of the microbiota, and the changes in the plasma proteome, would be accompanied by substantial and sustained changes in ponderal and linear growth. Here, we describe our protocols for POC trials designed to assess whether compared to RUSF, administration of MDCF-2 to larger numbers of children with MAM for longer periods of time will produce durable changes in the configurations of their gut communities, their plasma proteomes, anthropometric indicators of their growth, and their morbidities. Two cohorts of 12–18-month-old Bangladeshi children will be enrolled; one with primary MAM and the other with MAM after having been treated for severe acute malnutrition (post-SAM MAM). In each cohort, children will be randomized to one of two treatment arms; members of one arm will receive MDCF-2 while members of the control arm will receive a standard RUSF. Primary clinical outcome measures will be the rate of weight gain and the change in WLZ over the intervention period. Biospecimens (blood, feces and urine) collected before, during and after the intervention will be analysed to determine the extent of gut microbiota repair and the degree of improvement in levels of plasma biomarkers and mediators of healthy growth.

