### Aim and objectives

To determine whether daily, controlled administration of MDCF-2 for 3 months provides superior improvements in weight gain, microbiota repair, and elevated levels of key plasma biomarkers/mediators of healthy growth compared to the control RUSF formulation. The sustainability of microbiota repair, growth outcomes and physiologic state will be assessed over a period of 4 years through collection and analysis of fecal and blood samples every 6 months.

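### Durability over 4 years is an aim, but the arms are compared visit by visit at about nine post-feeding visits with single-time-point methods, and no contrast is named to decide it

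*Protocol article*

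**What the plan says.** The Data analysis plan says that "The two groups of children receiving MDCF-2 and RUSF in each trial will be compared at baseline and at different time points", and refers to Fig. 1 for the times. The Methods paragraph of the Abstract lists them: baseline, 1 month, then "at the end of intervention (3 months), 1 month after cessation of intervention, and every 6 months thereafter for 4 years".

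For the primary clinical outcome variables, the Data analysis plan names the t-test, Mann-Whitney, chi-square and Fisher's exact tests. It adds a multivariable linear regression for the anthropometric outcome, without linking it to a visit or describing it as a repeated-measures model.

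Durability is part of the purpose. Under Aim and objectives, "The sustainability of microbiota repair, growth outcomes and physiologic state will be assessed over a period of 4 years". The Background explains that the 1-month pilot was too short to show lasting change, and the Discussion says the follow-up allows durability to be assessed within and across arms.

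The Background confines the primary clinical outcomes to the feeding period: "Primary clinical outcome measures will be the rate of weight gain and the change in WLZ over the intervention period". The Sample size calculation rests on one WLZ comparison and states "then the sample size would be 49 in each arm at 80% power and 5% level of significance".

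**The concern.** Asking whether an effect lasts is one question about a trajectory. The plan addresses it with a series of comparisons, each confined to one visit. It does not say which visit, or which summary of the visits, answers the question.

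Two things are at stake. First, with about nine post-feeding results per outcome, one significant visit could be presented as evidence of a lasting effect and the rest as noise or fading. Equally, a real loss of effect could be obscured by one late significant visit. Second, separate tests do not combine the repeated measurements on the same child, so they are generally a less precise answer than one longitudinal contrast would be.

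The point concerns the number of visits for a single outcome. Testing several outcomes would come on top of it.

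**Working it through.** **The plan's own figure.** Inputs from the Sample size calculation: WLZ −2 to −1.7, so a difference of 0.3 (used as the difference between arms); SD 0.53; 80% power; 5% level. Sidedness is not stated, but two-sided reproduces the figure:

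n per arm = 2 × (1.960 + 0.842)² × 0.53² / 0.30² = 48.99, so 49.

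With 20% attrition: 49 / 0.80 = 61.25, so 62 per arm and 124 per trial. Both match. The trial is sized for one two-sided 5% test.

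**Counting visits.** From the Abstract: months 1 and 3 during feeding; 1 month after cessation (month 4); then every 6 months for 4 years (months 10 to 52), which is 8 visits. Post-feeding: 1 + 8 = 9. Post-baseline: 2 + 9 = 11. Fig. 1 is not shown. If the 4 years ran from enrolment, there would be about 8 post-feeding visits.

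**Chance of at least one significant visit.** One outcome, one trial, no true difference at any counted visit, each visit tested two-sided at 5%. If visits were independent, nine would give 1 − 0.95⁹ = 0.37, which is a ceiling. Visits on the same children are correlated. The protocol gives no correlation, so a range is assumed. Test statistics were simulated (400,000 draws) as Z_j = √ρ·U + √(1−ρ)·e_j, counting draws where any |Z_j| > 1.96:

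| Visits counted | ρ = 0.3 | 0.5 | 0.7 | 0.8 | 0.9 | 0.95 |
|---|---|---|---|---|---|---|
| 9 post-feeding | 0.33 | 0.27 | 0.20 | 0.17 | 0.12 | 0.10 |
| 8 post-feeding | 0.30 | 0.25 | 0.19 | 0.16 | 0.12 | 0.10 |
| 9, only results favouring MDCF-2 (nominal 0.025) | 0.17 | 0.14 | 0.10 | 0.08 | 0.06 | 0.05 |

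If correlation instead decays with the time between visits, the nine-visit figure is 0.31, 0.23, 0.18 and 0.13 for correlations of 0.6, 0.8, 0.9 and 0.95 per 6 months. All of these lie within the range above.

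**If month 3 had to be significant first.** Under no effect at any time, the chance of a significant month 3 together with at least one significant later visit is 3.8% to 4.5% (decay 0.6 to 0.9 per 6 months), so the inflation disappears. It returns where month 3 shows a true effect that has since vanished. If month 3 is then almost sure to be significant, the nine-visit rates apply nearly in full.

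**Comparing remedies.** One pre-named contrast keeps the 5% level. If 49 per arm are still evaluable and the SD is still 0.53, a comparison at one named visit has 80% power for a 0.3 difference. Bonferroni over nine visits (0.05 / 9 = 0.0056 each) would have 51% power per visit at 49 per arm, or need 82 evaluable per arm.

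**The case against.** The strongest objection is that this is a condensed article. Ranking visits, handling multiplicity and choosing a longitudinal model for a non-primary objective are often left to an SAP, which is not shown. That stands as far as the missing rule goes: its absence alone would not be a finding. The point survives because the article does commit itself. It fixes a set of comparison times and names methods, and those methods do not suit a stated aim.

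Second, the four tests are attached to the primary clinical outcome variables, which the Background limits to the feeding period. The sustainability sentence in the Aim also goes on to refer to stool and blood samples, which have their own analysis. Both are fair. But the same Aim sentence names growth outcomes, the Interventions section schedules post-feeding anthropometry, and no other between-arm method for those visits is given. The regression might serve, but nothing says that it uses repeated measurements.

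Third, a reader might infer that the plan would declare durability from any one significant visit. No section says so. The 10% to 33% is therefore conditional on a rule that the document leaves open, and on an assumed correlation.

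Fourth, a reader might infer that month 1 competes with month 3 as the efficacy test, because the Sample size calculation cites pilot data in which "the baseline WLZ score of children who received MDCF 2 was − 2.2 and after 1 month of supplementation was − 1.7". The documents do not support this. The pilot is only the source of the effect size, and the Abstract, Background and Aim all point to the 3-month feeding period.

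**Conclusion.** The concern holds in a limited form. The visit-by-visit approach is a poor method for the durability aim, and a better one is available at almost no cost. If any one significant post-feeding visit were allowed to support durability, the false-positive chance per outcome would be about 2 to 6.5 times the nominal 5% (10% to 33%) over exchangeable correlations of 0.95 to 0.3. It exceeds 5% at every correlation tried and barely changes with eight visits instead of nine. Its practical weight is greatest where an effect at month 3 is real but has not lasted, which is exactly what the follow-up is meant to detect.

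It should not be read as a flaw in the main efficacy result. The 3-month comparison remains one 5% test, and the stated 49 evaluable and 62 enrolled per arm reproduce.

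**What to change.** In the Sample size calculation and the Data analysis plan, confirm that the baseline-to-month-3 difference between arms decides efficacy, in line with the Background, and that month 1 is supportive.

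For anthropometric follow-up, replace the visit-by-visit tests with one repeated-measures mixed model per outcome, containing arm, visit, arm-by-visit and the baseline value. Name in advance one durability contrast from that model: either a chosen late visit or an average over a stated post-feeding window. The choice is the sponsor's; a long average can hide fading, and a single late visit uses less of the data. Test the contrast only if month 3 is significant.

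Report every individual follow-up visit as an estimate with a 95% interval, labelled exploratory, so that any fading stays visible.

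The cost is revised wording and a little more modelling, with no new visits, data or children. The trial gives up claims of significance at individual follow-up visits.
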